## Abstract

**Background:**

There are an estimated three million people in the United Kingdom with chronic obstructive pulmonary disease (COPD), and the incidence of bronchiectasis is estimated at around 0.1% but is more common in COPD and severe asthma. Both COPD and bronchiectasis are characterized by exacerbations in which bacteria play a central role. Pseudomonas aeruginosa is isolated from sputum samples from 4% to 15% of adults with COPD and is more likely to be isolated from patients with severe disease. Earlier detection of exacerbations may improve morbidity and mortality by expediting treatment. Aseptika Ltd has developed a system for patients to self-monitor important physiological measurements including levels of physical activity, peak flow, forced expiratory volume (FEV1), and biomarkers for P aeruginosa in sputum.

**Objective:**

We aim to test this system in 20 participants with *P aeruginosa* colonization and 10 controls with *Haemophilus influenzae*.

**Methods:**

We plan to recruit 30 adult participants with COPD or non-CF bronchiectasis who have cultured *P aeruginosa* or *H influenzae* during an exacerbation in the last 6 months. They must produce sputum on most days and should have been stable for 4 weeks prior to entry. Daily data collected will include symptoms, health care usage, medication, weight, FEV1, physical activity level, blood pressure, oxygen saturation, and temperature. Sputum and urine samples will be provided daily. These data will be analyzed to assess predictive value in detecting upcoming exacerbations. Qualitative data will be gathered through self-administered questionnaires and semistructured interviews to gather information on participant coping and their use of the technology involved.

**Results:**

Recruitment has been completed and results from the study should be available at the end of 2017.

**Conclusions:**

The SENSOR study aims to test a home-monitoring system in people with chronic airway infection and is currently underway.

## Introduction

### Overview

#### Burden of Respiratory Disease With Pseudomonas Aeruginosa

There are an estimated 3 million people in the United Kingdom with chronic obstructive pulmonary disease (COPD) [1]. Bacteria cause acute exacerbations that characterize the course of COPD, and these exacerbations are associated with substantial morbidity and mortality. In addition, bacteria are present in the lower airways of many adults with COPD, even during clinically stable periods, contributing to the airway inflammation that is a hallmark of COPD.

The observation that  *Pseudomonas aeruginosa* is isolated from sputum samples from 4% to 15% of adults with COPD in many cross-sectional studies [2-4] suggests that the bacterium is a relatively common cause of infection in this clinical context. *P aeruginosa* is more likely to be isolated from patients with severe disease [4], particularly among patients who require mechanical ventilation for severe exacerbations.

*P aeruginosa* may cause chronic infections in patients with COPD that are similar to those seen in patients with cystic fibrosis (CF). Strains of *P aeruginosa* that persist in the airways of adults with COPD demonstrate changes characteristic of chronic infection that are similar to changes observed in CF, supporting the conclusion that chronic  *P aeruginosa* infection occurs in the context of COPD.

The incidence of bronchiectasis in the United Kingdom is not certain. Chest x-ray reviews in the 1950s suggested an incidence of 100/100,000 with an increase in prevalence with age [5]. With the advent of advanced imaging techniques, up to 30% of patients with COPD and severe asthma are found to have features of bronchiectasis on computed tomography.

Within our center, exacerbations of COPD and bronchiectasis are managed through a combination of admission to a dedicated 76-bed unit and self-management by the patient/carer at home. Patients are provided educational literature, a care plan, and supplies of antibiotics and steroids for use at home. Patients are encouraged to recognize signs of exacerbation and to begin immediate treatment with antibiotics. They are requested to report when they have initiated antimicrobial therapy at home so this can be followed up within 2 days (but often do not report because they feel better). Best practice recommends that patients are followed up within 3 weeks after being admitted for exacerbation [1].

The Portsmouth Hospitals Trust (PHT) Respiratory Centre has created a culture of empowering patients through education and by transferring the skills required for self-management so as to reduce rates of admission [6]. The costs of providing skilled community staff for home visits has proved uneconomic but the cost burden of unscheduled admissions is equally high, necessitating innovative solutions to assist patients to self-manage.

Aseptika Ltd has developed a system for patients to self-monitor important physiological measurements including levels of physical activity, weight, peak flow, forced expiratory volume (FEV_1_) blood oxygenation, heart rate, wellness scores, clinical contacts diary, start of antibiotics and steroids, and 1 to 3 biomarkers of virulence of *P aeruginosa* in sputum. In a clinical trial sponsored by Papworth Hospital during 2013, data were collected by 15 CF participants and uploaded electronically to Activ8rlives, a Web-based data collection and viewing system developed by Aseptika. The study indicated that clinical parameters and sputum biomarker changes are likely to enable early detection of exacerbations in CF patients and have a role in highlighting treatment failure [7]. The Self-Management Checks to Predict Exacerbations of *Pseudomonas Aeruginosa* in Patients with Long-Term Respiratory Conditions (SENSOR) study aims to investigate if these tools can be more widely applied to other respiratory conditions such as COPD and non-CF bronchiectasis (NCFB). The Activ8rlives app operated from an iPad tablet uses wireless connectivity to home-use monitors to upload physiological and subjective scores and diary information directly to the Cloud-based Activ8rlives solution. The differing demographics between this study population and the Papworth population (ie, the older age of the Portsmouth population) will enable us to learn whether older patients with long-term conditions can be trained to use these monitoring devices.

#### Rationale for Study and Potential Impact

As described above, initial trials with Activ8rlives system with CF patients indicated a potential role of this technology in improving patient monitoring and self-management. This is particularly important in patients with chronic respiratory conditions for whom the staff-to-patient ratio is typically much lower than CF and for whom innovative solutions to better enable patients to monitor and self-manage their own condition are key to keeping their illness under control.

It is hoped that the results of this study will enable the self-care planning process that currently exists at PHT to be supported with the Activ8rlives technology to extend the effectiveness of our home hospital concept. Qualitative feedback from patients and carers will contribute to the continuing improvement and adaptation of the system.

The eventual addition of the Activ8rlives self-monitoring solution (including tests for sputum *P aeruginosa* virulence) as an assist for the patients and clinical staff and the provision of an information technology (IT) infrastructure for staff, which could simultaneously monitor and mentor many thousands of patients with respiratory conditions in the Portsmouth area without the costs incurred through undertaking face-to-face home visits, would have a significant impact both on patient health and National Health Service (NHS) costs. The development of this infrastructure and subsequent assessment of the effectiveness and cost effectiveness of the system would be assessed in a further large-scale randomized controlled trial.

### Aims and Objectives

#### Primary Objective

To use longitudinal *P aeruginosa* sputum biomarker, telemetry, and symptom data to develop individualizable models to predict a *P aeruginosa* exacerbation in chronic non-CF respiratory disease

#### Secondary Objectives

To investigate the correlation between *P aeruginosa* biomarkers and telemetry with clinical outcomes during and after treatment of an exacerbation with antibioticsTo describe rates of adherence to data input by participants/carersTo explore whether the self-management platform provided for data upload is feasible and acceptable for daily use in this clinical populationTo pilot questionnaires to collect data on health care use in this population

#### Exploratory Objectives

To collect urine samples for future studies that may explore whether biomarkers present in urine can also contribute additional information to the exacerbation prediction modelTo perform molecular analysis for the *Haemophilus influenzae* group to corroborate microbiological tests in control groups.

## Methods

### Overview

In a mixed methods study, a longitudinal cohort of participants and their carers (where appropriate) will be asked to collect physiological, biological, and disease outcome data over a 6-month period. Neither participants nor the clinicians responsible for participant care will have access to the longitudinal data, and this information will not be used to make clinical decisions. The laboratory samples will be analyzed in a blinded manner. These data will then be analyzed to develop a model for predicting onset of exacerbations that can be built into a self-monitoring system.

Qualitative methods will be used to explore participant and carer experiences of using the technology and performing daily self-monitoring assessments. The expected duration of participation in the cohort will be 6 months, with an invitation to complete a self-administered questionnaire at baseline to inform a face-to-face semistructured interview with patients with or without carer joint participation at the end of the follow-up period.

### Primary and Secondary Endpoints and Outcome Measures

#### Primary Endpoint

An exacerbation will be defined as the initiation of antimicrobial therapy for respiratory symptoms either at home or on admission, with or without concomitant steroids or admission. For participants who are already on continuous antibiotics, an exacerbation will be defined as starting a course of different antibiotics or increasing the dose or frequency of existing antibiotics due to increased symptoms.

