### Study Participants

#### Inclusion Criteria

The participant must meet all of the following criteria to be considered eligible for the study:

Male or female, aged 18 years or aboveDiagnosed with at least one (or a combination) of COPD and non-CF bronchiectasisTwo or more exacerbations with the same pathogen (*P aeruginosa* or *H influenzae*) proven on culture and treated with antibiotics within the last 12 months, one of which must have been within the last 6 monthsExacerbation-free for the previous 4 weeksProducing at least 1 mL of sputum dailyMust be capable of operating the self-monitoring devices and tablet-based IT system or have a carer capable of undertaking the measurements and collection, storage, and transport of samplesWilling and able to give informed consent for participation in the study

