#### Clinic Visits

Participants will be required to attend the clinic for a follow-up visit at months 3 and 6 (study completion) ± 2 weeks. Participants will attend their normal review with the medical team that usually involves lung function, sputum sample for culture, and clinical review. They will then have a research visit which will involve disease-specific control and quality of life questionnaires (Quality of Life–Bronchiectasis, Short Form Health Survey, St. George's Respiratory Questionnaire, EuroQol 5-Dimension Questionnaire) as well as noting any changes to treatment and exacerbations. The data collected from these visits will be recorded on paper CRFs which will then be uploaded by a member of the research team to a local study database with restricted access.

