### Data Analysis

#### Description of Analysis Populations

The study is a nonrandomised cohort of a single group of patients. All subjects recruited into the study will be included in the data analysis.

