#### Analysis of Endpoints

The first stage of the data analysis is to use data on the collected parameters (eg, peak flow, pulse rate, oxygen saturation, activity data) to predict when an exacerbation is likely. Control charts will be used to determine the boundaries of normal behavior for each parameter. Separate control charts will be used for each participant, as what constitutes normal behavior will vary from participant to participant. When a parameter strays from normal behavior (eg, exceeds 99% control limits), an exacerbation will be predicted.

To examine the association between predicted exacerbation and actual exacerbation, participant follow-up will be divided into periods of time (eg, 7-10 days). A comparison of actual exacerbation when exacerbation has and has not been predicted will be made. To allow for the repeat measurements over time from the same participants, the analysis will be performed using multilevel logistic regression. Additionally, the sensitivity and positive predictive value of the predictions will also be calculated. Estimated values will be presented along with corresponding confidence intervals. Further exploratory analysis using novel computing methods will be conducted.

Health care use data will be presented descriptively (eg, the frequency and type of health care contacts over the study period for different participant groups).

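### The primary objective is to predict P aeruginosa exacerbations, but the endpoint counts antibiotic starts of any cause and the primary analysis as written pools the H influenzae controls

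*Protocol article*

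**What the plan says.** In the protocol article, the Primary Objective section aims "to develop individualizable models to predict a *P aeruginosa* exacerbation in chronic non-CF respiratory disease". The study's full name points to the same organism.

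The Primary Endpoint section says: "An exacerbation will be defined as the initiation of antimicrobial therapy for respiratory symptoms either at home or on admission". Steroids or a hospital stay may accompany the event but are not needed. For participants on continuous antibiotics the event is "starting a course of different antibiotics or increasing the dose or frequency of existing antibiotics due to increased symptoms". Neither branch mentions an organism.

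Microbiological proof belongs to entry: under Inclusion Criteria, earlier exacerbations must have been "proven on culture and treated with antibiotics within the last 12 months". In follow-up, culture appears only under Clinic Visits, at months 3 and 6, within the "normal review with the medical team that usually involves lung function, sputum sample for culture, and clinical review". It is not tied to the onset of an event.

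Sampling and Sample Size divides the 30 participants into 20 with chronic P aeruginosa infection and 10 with H influenzae. The abstract's objective calls the latter controls. Description of Analysis Populations says: "The study is a nonrandomised cohort of a single group of patients. All subjects recruited into the study will be included in the data analysis". The section on the analysis of endpoints then states: "A comparison of actual exacerbation when exacerbation has and has not been predicted will be made", using multilevel logistic regression. It names no organism or group term. Participant groups are mentioned there only for the descriptive health care use data.

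**The concern.** The event named in the objective and the event counted by the endpoint are different. An antibiotic start prompted by another bacterium, by a virus or by caution counts fully, and the same definition serves the H influenzae participants. The Introduction adds that patients hold antibiotics at home, are encouraged to start them promptly and often do not report it. Many events may therefore have no microbiology at all.

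What is at stake is the conclusion, not whether the data are usable. A clear association between alarm and exacerbation would invite the claim that P aeruginosa exacerbations can be predicted. Yet it could arise from general deterioration picked up by pulse, peak flow or activity, in either group. A weak association for the sputum biomarkers would be just as hard to read: the marker may have failed, or the events may have had other causes.

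**Working it through.** **Inputs**, all from Sampling and Sample Size: exacerbation in 60% of predicted and 10% of other periods; a prediction in 1 of 12 periods; 5% significance and 90% power; 12 periods per participant; intraclass correlation 0.18; 20 P aeruginosa and 10 H influenzae participants.

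1. **The plan's own figure.** Two proportions, two-sided (sidedness is not stated), allocation 1:11, pooled rate (0.6 + 11 × 0.1)/12 = 0.1417.
   - Predicted periods needed: [1.96 × √(0.1417 × 0.8583 × 12/11) + 1.2816 × √(0.6 × 0.4 + 0.1 × 0.9/11)]² / 0.5² = 7.31.
   - With continuity correction: (7.31/4) × [1 + √(1 + 2 × (12/11)/(7.31 × 0.5))]² = 9.37, rounded up to 10. Total 10 × 12 = 120 periods.
   - Design effect: 1 + 11 × 0.18 = 2.98, about 3. 120 × 3 = 360 periods, and 360/12 = 30 participants.

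   The stated 120, 360 and 30 reproduce, and the H influenzae controls are counted within the 30.

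2. **Events expected.** Overall rate: 0.6 × 1/12 + 0.1 × 11/12 = 14.2% per period. In 360 periods: 51 events.

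3. **Events by group.** The article gives no rate by group. If the H influenzae rate is k times the P aeruginosa rate, the H influenzae share is 10k/(20 + 10k).
   - k = 1 (equal rates): 10/30 = 33%, so 17 of 51 events, leaving 34 in the P aeruginosa participants.
   - k = 0.5: 5/25 = 20%, about 10 events.
   - k = 1.5: 15/35 = 43%, about 22 events.

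4. **What the endpoint can say about the 34.** P aeruginosa participants contribute 20 × 12 = 240 periods. Of these, 20 carry a prediction (20 × 0.6 = 12 events) and 220 do not (220 × 0.1 = 22 events). The endpoint does not show which of the 12 or the 22 were due to P aeruginosa.

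5. **How precise a group contrast would be.** Apply the plan's rates to both groups.
   - P aeruginosa: 12 events and 8 non-events with an alarm, 22 and 198 without. Variance of the log odds ratio: 1/12 + 1/8 + 1/22 + 1/198 = 0.259.
   - H influenzae: 6 and 4 with an alarm, 11 and 99 without. Variance: 1/6 + 1/4 + 1/11 + 1/99 = 0.518.
   - Ratio of the two odds ratios: standard error √0.777 = 0.88, so the 95% interval runs a factor of exp(1.96 × 0.88) = 5.6 either way.
   - With the full design effect: √(0.777 × 2.98) = 1.52, a factor of about 20. This is probably pessimistic, because alarms vary within a participant.

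6. **The 20 P aeruginosa participants alone.** 240/3 = 80 effective periods. At 60% against 10%, power is about 88% by the normal approximation, compared with 96% at 120. By Fisher's exact test it is 77% to 82% (6 or 7 predicted periods of 80), compared with 94% at 10 of 120.

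**The case against.** The strongest reply is that the design already leans towards P aeruginosa. Entry needs repeated culture-proven exacerbations with one pathogen, the 20 participants are described as chronically infected, sputum is stored daily for P aeruginosa biomarkers, and a control group was recruited. The article is condensed and refers to a statistical analysis plan that is not shown, where a between-group term could sit. The abstract's methods, the Methods overview and the Discussion speak of exacerbations in general. An antibiotic-start endpoint is also a reasonable pragmatic choice.

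Much of this stands. It means that a reader should not infer that the study is unable to yield any organism-specific evidence. The limit applies to the primary analysis as written, and the absence of a contrast here does not prove that none is planned. It does not remove the mismatch: objective and endpoint are both fixed in this article, and they name different events.

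A reader might also infer that events of other causes cap biomarker sensitivity, for example at 50% to 70% if 30% to 50% of events are not due to P aeruginosa. The document does not support that. It gives no such share. Its own rates imply a sensitivity of 12/34 = 35%, already below that cap. The objective also combines biomarkers with telemetry and symptoms, which can flag events of any cause.

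Nor would routine cultures settle attribution. The Introduction says bacteria are present in stable periods too, so a positive culture in a chronically infected patient does not show cause. Events treated at home would often have no culture.

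**Conclusion.** The point holds for the primary analysis as written. The objective names a P aeruginosa exacerbation, the endpoint counts any antimicrobial start or change for respiratory symptoms, and all participants are analysed together with no stated organism contrast. About 17 of 51 expected events, one third, would come from participants enrolled for H influenzae. That figure assumes the plan's rates and equal rates in the two groups; a relative rate of 0.5 to 1.5 gives 20% to 43%. The mismatch itself depends on no assumed figure. The sample-size arithmetic is not at fault, and the endpoint need not be replaced. What needs correcting is the claim the analysis is allowed to support.

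**What to change.** - Restate the primary objective and the permitted conclusion as antibiotic-treated respiratory exacerbation in people with chronic P aeruginosa infection.
- Report the association between alarm and exacerbation separately for the 20 P aeruginosa and the 10 H influenzae participants, for biomarker alarms in particular. Give the group-by-alarm interaction with its confidence interval in the multilevel logistic model already planned.
- Make any organism-specific claim depend on that contrast.

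Cost: a change of wording and one extra model term. No new participants, visits or samples are needed, which matters because recruitment is complete. As the article says analysis is under way, the contrast should be documented as an addition unless the statistical analysis plan already holds it.

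Downsides: the claim becomes narrower. With 10 controls the interaction will be imprecise, and more so if biomarker alarms are rarer than 1 in 12 periods in that group. An interval that includes no difference would not show that the groups behave alike. The estimate for the P aeruginosa participants alone rests on 240 periods rather than 360, with the loss of power shown above.

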#### Secondary Endpoints

Treatment efficacy will be defined as the day at which antibiotic treatment for that episode is completed.

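### The primary event is each antibiotic start with no episode rule, and treatment and recovery periods stay in the comparison, so ongoing illness can distort the predictive estimates in either direction

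*Protocol article*

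**What the plan says.** **Event.** Under Primary Endpoint: "An exacerbation will be defined as the initiation of antimicrobial therapy for respiratory symptoms either at home or on admission". Steroid use and hospital admission do not alter this. A second rule covers only the subgroup on continuous antibiotics, for whom the event is "starting a course of different antibiotics or increasing the dose or frequency of existing antibiotics due to increased symptoms".

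**Episode.** Under Secondary Endpoints: "Treatment efficacy will be defined as the day at which antibiotic treatment for that episode is completed". This gives an episode an end, but no section says when a new one may begin. The Inclusion Criteria ask for four weeks without an exacerbation, at entry only.

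**Analysis.** Under Analysis of Endpoints, each participant has a control chart for each parameter: "When a parameter strays from normal behavior (eg, exceeds 99% control limits), an exacerbation will be predicted". Then "participant follow-up will be divided into periods of time (eg, 7-10 days", and actual exacerbation is compared between predicted and not-predicted periods by multilevel logistic regression, with sensitivity and positive predictive value (PPV) also reported. No periods are set aside because the participant is under treatment or recovering.

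**Purpose.** The Overview of the Methods states that the model is meant to predict the onset of exacerbations.

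**The concern.** The aim is onset, but the event is a treatment start. If a first course fails and another is started in a later period, the endpoint as printed can count two exacerbations from one illness. The second is not an onset.

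The periods in which this happens are also those in which measurements are likely to be abnormal because the participant is ill. The Introduction says that the earlier cystic fibrosis study suggested these signals help to show treatment failure. Under the control-chart rule, a flag in such a period is a correct prediction if a restart falls there and a false alarm if it does not. Neither says anything about early warning.

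Sequential starts are foreseeable, since the Introduction describes antibiotics held and started at home alongside admission to a dedicated unit. The multilevel model allows for participants differing in their overall event rate. It does not join two starts of one illness or remove periods in which a new onset could not occur.

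At stake are the three quantities that will be read as the performance of the monitoring system: the odds ratio, sensitivity and PPV.

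**Working it through.** **1. The plan's own figure (Sampling and Sample Size).** Inputs: 60% against 10%, one period in 12 predicted (ratio k = 11), 5% significance, 90% power. The plan does not state sidedness; two-sided with continuity correction reproduces it.
- Uncorrected, with pooled proportion (0.6 + 11×0.1)/12 = 0.1417: n = [1.96√(12/11 × 0.1417 × 0.8583) + 1.2816√(0.24 + 0.09/11)]² / 0.5² = 7.3 predicted periods.
- Corrected: (n/4)[1 + √(1 + 2(k+1)/(n·k·0.5))]² = 9.4, rounded up to 10. Then 10 × 12 = 120, as stated.
- Design effect 1 + 11×0.18 = 2.98; 120 × 2.98 = 357.6, stated as 360; 360/12 = 30 participants.

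The sample size reproduces, and the present point does not alter it.

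**2. Planning table.** Of 360 periods, 30 are predicted (18 with an event, 12 without) and 330 are not (33 with, 297 without). That is 51 events, sensitivity 18/51 = 35%, PPV 18/30 = 60%, odds ratio (18×297)/(12×33) = 13.5.

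**3. Assumptions.** The protocol gives no retreatment rate. Take the 51 events as first starts, each followed by one post-start period that the planning table held as unflagged and event-free. In a share r of these (10, 20 or 30%) there is a restart: x = 51r = 5.1, 10.2 or 15.3. Flag and event are scored in the same period.

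- **A, only restart periods flagged:** cells 18+x, 12, 33, 297−x.
- **B, every post-start period flagged:** cells 18+x, 12+(51−x), 33, 246.
- **C, post-start periods excluded:** cells 18, 12, 33, 246; 360 − 51 = 309 periods; odds ratio (18×246)/(12×33) = 11.2.

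| | r = 10% | r = 20% | r = 30% |
|---|---|---|---|
| A: odds ratio | 17.0 | 20.4 | 23.7 |
| A: PPV | 66% | 70% | 74% |
| B: odds ratio | 3.0 | 4.0 | 5.2 |
| B: PPV = (18+x)/81 | 29% | 35% | 41% |
| A and B: sensitivity = (18+x)/(51+x) | 41% | 46% | 50% |
| C: odds ratio / PPV / sensitivity | 11.2 / 60% / 35% | same | same |

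Worked example at r = 20%: A is (28.2×286.8)/(12×33) = 20.4; B is (28.2×246)/(52.8×33) = 4.0.

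**4. When the direction changes.**
- Sensitivity: if a share p of restart periods is flagged, (18+px)/(51+x) exceeds 18/51 exactly when p > 18/51 = 35%.
- PPV: let all restart periods and a share g of the other post-start periods be flagged. PPV exceeds 60% only if r/(r + g(1−r)) > 0.6, that is g < (2/3)·r/(1−r) = 7%, 17% or 29% for r = 10, 20 or 30%.
- Odds ratio against C: with y = g(51−x), set (18+x)(297−x−y) = (12+y)(18×246/12) = 369(12+y). This gives y = 5.9, 9.2, 12.3, so g = 13%, 23%, 34%. Below that the odds ratio is too high, above it too low.

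**5. If the monitor had no predictive value.** With 30 flags independent of 51 events, the cells are 4.25, 25.75, 46.75, 283.25 and the odds ratio is 1.0. Under A it becomes 2.2/3.3/4.4, or 1.5/1.9/2.3 if half of the restart periods are flagged. Under B it is 0.65/1.08/1.58, against 0.82 under C.

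C differs from 13.5 and from 1.0 because this construction removes only unflagged, event-free periods. So 11.2 and 0.82 are reference values within the illustration, not true effects.

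**The case against.** A reader might infer that every antibiotic start, switch or escalation counts for everyone, and that sensitivity, PPV and the odds ratio are therefore all inflated. The documents do not support this:

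- Switch and escalation are named as events only for participants on continuous antibiotics, and only for increased symptoms. For others the event is an initiation, and whether a mid-course change is one is unclear.
- Logistic regression implies a yes/no outcome per period, so two starts within one period give one positive period. Double counting needs a restart in a later period.
- The predictor is a control-chart deviation, not a previous exacerbation. An earlier start can raise the chance of a flag only through measurements that are still abnormal.
- If measurements usually stay outside limits after a start, most post-start periods are flagged and, at these retreatment rates, most of those flags are false alarms. Scenario B then applies, and PPV and the odds ratio fall.

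All four points stand, and they limit the claim.

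Two further points stand only in part. The secondary endpoint's "the day at which antibiotic treatment for that episode is completed" allows an episode to be read as running from start to completion of treatment. But the primary endpoint does not use that reading, and it does not settle whether a course begun soon after completion is new. An episode rule may also sit in the full protocol or in the statistical analysis plan, neither of which is shown. Even so, the published text fixes the event as an initiation and divides follow-up with no exclusion; followed as printed, it has the effect described.

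**Conclusion.** The concern holds in this form: the primary event has no boundary between a new exacerbation and retreatment of the same one, and treatment and recovery periods stay in the comparison. The estimates then mix ongoing illness with prediction of onset.

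Sensitivity is inflated if restart periods are flagged more often than 35%. PPV and the odds ratio can be biased either way: 17/20/24 or 3.0/4.0/5.2 at an assumed 10/20/30% retreatment, against 11.2 with post-start periods excluded. A general claim of inflation is not supported. Nor does the uncertain direction rescue the plan, since it means that neither a high nor a low odds ratio could be read as the system's performance at onset.

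The sizes rest on the planning values, on retreatment rates that the protocol does not give, and on one post-start period per first start. The two scenarios are the extremes of flagging after a start when every restart period is flagged. A change to the analysis definition should be made; the sample size derivation is unaffected.

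**What to change.** For analysis only, with no bearing on how participants are treated:

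- Count the first start of an episode as the onset event.
- Treat later starts, and changes of antibiotic, dose or frequency, as part of the same episode until a stated interval has passed. The investigators should set its length before the data are examined. The four weeks in the Inclusion Criteria are an internal reference, but they are an entry criterion and not an episode rule.
- Remove periods within an ongoing episode from the at-risk set for the odds ratio, sensitivity and PPV.
- Report the analysis of all initiations over all periods as a sensitivity analysis.

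The Results section says that the study is already in data analysis. If the interval is chosen after alarms and events have been compared, it should be declared as a deviation, as the protocol's own section on deviations requires.

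**Cost.** No new data: Data Management already has antimicrobial starts entered, and the secondary endpoint needs completion dates. The price is fewer events and periods, and so somewhat lower precision. About 309 of 360 periods remain if one is removed per first start. Four weeks is 2.8 ten-day periods, so that interval could remove up to about 51 × 2.8 = 143, before overlap between episodes and the end of follow-up reduce the number. The loss should be weighed when the interval is chosen.
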